### Study drug

Patients in the experimental group received a standard dose (10 mg daily) of dapagliflozin in addition to the standard and optimized heart failure regimen, while patients in the control group received the standard and optimized heart failure regimen alone. Subjects will be advised to take the study drug at the same time everyday according to approved instructions.

### Outcomes

#### Primary outcome

The primary endpoint of the trial is the AHI change determined by nocturnal polygraphy, before and after 3 months of treatment with dapagliflozin. The 2012 American Academy of Sleep Medicine recommendations are used to characterize apnea and hypopnea events, the phenotype, whether central, obstructive, or mixed.

#### Secondary outcomes

The proportion of patients with a 20% decrease in their AHI, before and after dapagliflozinThe proportion of patients with a 50% decrease in their AHI, before and after dapagliflozinEpworth Somnolence Scale (ESS) score before and after treatmentEchocardiographic measures of structure and function before and after dapagliflozin [ejection fractions, left ventricular diameters, atrial surface, diastolic function (strain), and filling pressures]Serum BNP and pro-BNP concentrations before and after dapagliflozinLaboratory testing also included creatinine, potassium, sodium, hemoglobin, and alanine and aspartate transaminaseQuality of life as measured by the Minnesota Living with Heart Failure Questionnaire and EQ-5D-3L Questionnaire, before and after dapagliflozinLevels of inflammatory and oxidative stress factors IL-6, CRP before and after dapagliflozin

### Adverse events

The adverse events will be investigated by open questions, including general symptoms, and by specific questions regarding symptoms potentially related with the drugs used in the trial, as hypotension, frequent urination, urgent urination, fatigue, loss of appetite, nausea, vomiting, etc. The rate of adverse effects will be determined by comparing the frequency of adverse events in the experimental group and control group. The criteria for discontinuing the trial for an individual participant are as follows:Those who have serious adverse reactions in the study and are not suitable to continue to participate in the studyDuring the study period, the participants had other acute and severe diseases and needed to take emergency measures

(The reasons and time of withdrawal from the study will be recorded in detail. Participants who have exceeded 1/2 of the course of treatment will be included in the curative effect analysis.)

Researchers will do their best to prevent possible dangers caused by this study. If adverse events occur, the medical expert committee will identify whether they are related to drug treatment or research process. The project will provide treatment expenses and corresponding economic compensation for the damage related to the trial in accordance with the Criterions for the Quality Control of Clinical Trial of Drugs.

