### Follow-up and duration of the study

There will be two visits at the clinical research center, one before (baseline) and one after (3 months follow-up) the dapagliflozin intervention. Data collection to assess efficacy of the intervention will be managed by research team members. An overview of the measures used at each of the four time points is illustrated in Table 2. For improving the compliableness of patients, the strategies are as follows: (1) adhere to the principle of voluntary participation and explain the benefits of this study to the participants and the importance of treatment and adherence to the treatment. Health education process could increase the related knowledge, change the behavior, and enhance the compliance of patient. (2) Written informed consent will be obtained from each patient before they begin the trial. All participants will fill in informed consents. (3) The treatment is free for participants, such as the relevant examination expenses and the telephone bill, traffic expenditures, and analgesic drugs incurred during the treatment and follow-up. (4) Record participants’ contact methods in detail, including mobile phone, WeChat, and e-mail for contact and follow-up.

**Table 2 Tab2:** Administration of study measures by assessment period

Research phase	Screening and randomization	Treatment period		
Interview	1	2	3	4
Research date	− 7–0	28 ± 2	56 ± 4	84 ± 6
Baseline information				
Informed consent	●			
General information	●			
History	●			
Physical examination	●	●	●	●
Treatment				
Inclusion/exclusion criteria	●			
Combined medication	●	●	●	●
Compliance		●	●	●
Completion of research				●
Inclusion/exclusion criteria				
PSG	●			
Echocardiography	●			
Security index				
Blood routine	●			●
Urine routine	●			●
Blood biochemical	●			●
Electrocardiogram	●			●
Adverse event assessment		●	●	●
Outcome				
AHI	●			●
Epworth Somnolence Scale (ESS)	●	●	●	●
Echocardiography	●			●
NT-proBNP	●			●
Quality of life as measured by the Minnesota Living with Heart Failure Questionnaire	●	●	●	●
EQ—5D—3L				
L_SpO2_	●			●
Inflammatory factors	●			●

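### Serious reactions and acute illness end study participation in either arm, not just dapagliflozin, so day-84 safety data and later adverse-event enquiries would be lost for health-related reasons

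*Protocol article*

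**What the plan says.** The Adverse events section of the protocol article opens its list with "The criteria for discontinuing the trial for an individual participant are as follows". The first criterion covers those "who have serious adverse reactions in the study and are not suitable to continue to participate". The second applies when "the participants had other acute and severe diseases and needed to take emergency measures". A parenthesis follows: "The reasons and time of withdrawal from the study will be recorded in detail", and "Participants who have exceeded 1/2 of the course of treatment will be included in the curative effect analysis". Neither criterion is limited to one arm. The Study drug section says that "patients in the control group received the standard and optimized heart failure regimen alone".

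Table 2 (section Follow-up and duration of the study) has visits at day -7 to 0, 28±2, 56±4 and 84±6. The safety rows for blood, urine, "Blood biochemical" and electrocardiogram are marked at the first and last visit only. "Adverse event assessment" is marked at days 28, 56 and 84, and physical examination at all four visits.

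Statistical methods promises both intention-to-treat and per-protocol analyses and rules out imputation. Secondary outcomes includes the laboratory values. Adverse events also says that event frequency will be compared between the two groups.

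**The concern.** The criteria speak of the trial and the study, not of the drug. Nothing in the section lets a patient stop dapagliflozin and remain under observation. Control patients take no study drug, so for them the rule can only mean leaving.

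Followed as written, patients who become seriously ill stop contributing data because they became ill. Their day-84 laboratory and ECG values are missing for health-related reasons, and an analysis that only leaves missing values out cannot make up for tests that were not done. Adverse events are then counted over shorter time in patients who were removed. The Discussion states that there is neither placebo nor double blinding, so the judgement that a patient is unsuitable to continue is made with the arm known. Removals could therefore differ between arms for reasons other than the event itself.

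**Working it through.** **1. What the rule ends.** Three wordings bear on this. The introductory line is about discontinuing the trial. The first criterion asks whether the patient can go on in the study. The parenthesis records withdrawal from the study. All three point to the study, and none mentions stopping treatment alone. Study design uses the same model for ventilator use: patients who need one leave the study.

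**2. What a withdrawn patient loses under Table 2.** Post-baseline laboratory tests and ECG exist only at visit 4, nominally day 84. That holds for every participant, so what withdrawal adds is the loss of this one set. Adverse-event enquiries fall on days 28, 56 and 84. On nominal days, with withdrawal at day t after any visit due that day, observation lost = 84 − t days:

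| Withdrawal at day t | Enquiries lost (of 3) | Days lost | Share of 84 days |
|---|---|---|---|
| 1 to 27 | 3 | 83 to 57 | 99% to 68% |
| 28 to 55 | 2 | 56 to 29 | 67% to 35% |
| 56 to 83 | 1 | 28 to 1 | 33% to 1% |

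The window for visit 4 opens at day 84 − 6 = 78. A patient leaving from day 78 on may already have had the final tests, so the smallest losses in the last row need not occur.

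**3. Size of an arm.** The Sample size section gives a difference of 8, an SD of 6, 90% power, 5% alpha, 20% loss and 30 patients. Taking the test as two-sided (the article does not say) with the normal approximation:

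n per arm = 2 × (1.960 + 1.282)² × 6² / 8² = 11.8, rounded up to 12. The total is 24, and 24 / (1 − 0.20) = 30.

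The plan's figure is reproduced if 30 is the total, which at 1:1 is about 15 per arm. The alternative reading, 30 per arm, is shown as well.

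**4. Day-84 coverage.** The number of removals is not given, so k = 1, 2 and 3 in one arm are assumptions. Coverage = (n − k) / n:

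| n per arm | k = 1 | k = 2 | k = 3 |
|---|---|---|---|
| 15 | 93.3% | 86.7% | 80.0% |
| 30 | 96.7% | 93.3% | 90.0% |

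**5. Observation time.** An arm of 15 has 15 × 84 = 1260 patient-days. Three removals lose between 3 × 1 / 1260 = 0.2% and 3 × 83 / 1260 = 19.8% of them, depending on timing.

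**The case against.** The strongest reply is that this is a journal article. Protocol version 2.0 is not shown and may well contain an exit assessment and follow-up after withdrawal. That stands: the lack of an exit column in Table 2 is no finding. A reader might also infer that the article says follow-up stops at withdrawal. No sentence does. The half-course rule hints the other way. Half of 84 days is day 42, and including patients who left after it in the efficacy analysis makes sense only if something is measured at or after leaving. The rule names no safety test, however.

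Two more inferences go too far. One is that withdrawn patients have no post-baseline safety data. Physical examinations and enquiries completed at days 28 and 56 remain, and the event that led to withdrawal still counts. The other is that withdrawal causes the gap in laboratory tests and ECG between baseline and visit 4, which Table 2 gives to everyone.

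It is also fair that the criteria are narrow. A patient with a serious reaction who is still suitable stays in. Statistical methods expects little attrition, and three of 15 equals the 20% loss already allowed for, so lost power is not the issue.

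What survives is the stated rule. It makes two health events reasons to leave the study, in both arms, where stopping the drug would do.

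**Conclusion.** The point holds in limited form, with medium confidence, and the text should be changed. As written, the two criteria turn a safety event into loss from the study. On a plain reading, this removes the day-84 laboratory and ECG set and the remaining enquiries for reasons linked to health. That does not fit the promised intention-to-treat analysis without imputation, and it compares adverse-event frequency over unequal time.

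The size cannot be fixed from the article. The coverage and patient-day figures illustrate one to three assumed removals and run from negligible to substantial. A reader might conclude that the rule flatters dapagliflozin. The article supports no direction, because it gives no event rates and the criteria apply to both arms. The conclusion assumes that the full protocol does not already separate stopping the drug from leaving follow-up.

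**What to change.** In Adverse events, make the two events criteria for stopping dapagliflozin in the experimental arm, and state that no control patient leaves follow-up because of them. For both arms, unless consent is withdrawn:

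- Keep the patient in the remaining scheduled visits, including the day-84 assessments where feasible.
- Continue adverse-event enquiries to day 84, by telephone if needed.
- If day 84 will not be attended, do the planned safety set at exit and report it as safety data. Values taken around an acute event do not replace the 3-month outcome value.
- Report adverse events in all randomised patients, with observation time by arm.

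If the full protocol already provides this, a clarifying sentence in this section is enough.

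The cost is an amendment of wording, for which Ethics approval describes a route; Trial status says that enrolment was still open at submission. Per affected patient, at most three enquiries already planned are kept, using contact details that the trial already collects. No new type of test is needed. The downside is a few contacts with patients who are ill or off treatment.

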**Fig. 1 Fig1:**
[figure not shown]
Study design overview

Patients will be divided into two groups:Group 1: patients received optimized heart failure therapy plus dagaglizin 10 mg daily, dapagliflozin will be started the day after the polygraphyGroup 2 (control group): patients received only optimized heart failure therapy

“Optimal drug therapy” in large heart failure trials usually refers to a combination of BBL, ACE inhibitors or ARBs and MR antagonists, with an optimal dose [23]. After 3 months of treatment, the final evaluation will include physical examination, echocardiography, laboratory testing, Minnesota Living with Heart Failure Questionnaire and EQ-5D, Epworth Sleepiness Scale, and nocturnal ventilatory polygraphy for all patients included in the study. During the research process, the participants cannot take other types of SGLT2 inhibitors such as empagliflozin and canagliflozin. Using ventilators to treat sleep apnea is not allowed; if it is necessary, they will withdraw from the study.

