### Sample size

The sample size calculation for this trial was performed using the PASS 11.0 program [25]. The primary end point of the main study was the decreasing value of Apnoea–Hypopnoea Index (△AHI). Based on existing data, a 8 ± 6 events/h change in AHI events/h between the control and therapy groups was considered clinically relevant (assuming that AHI would not change in the control group) [26–28]. Based on a power of 90% and an alpha value of 5%, it was calculated that a sample size of 30 patients (considering the 20% sample loss rate) would be sufficient to detect a difference in the effect size of at least 10%. Data monitors from the two centers will supervise the study process at a fixed period.

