### Statistical methods

Outcomes will be analyzed by intention-to-treat and per-protocol. A low attrition rate is expected, since the interventions are of short duration and minimal risk. Missing data will be considered as missing. Data imputation will not be employed. Normally distributed data will be presented as means and standard deviation. Non-normally distributed data will be displayed as median and interquartile range. The significance of the differences between two groups will be tested by chi-squared test for categorical variables and t test for measurement data. Results with a *P* value lower than 0.05 for alpha error will be considered statistically significant. Statistical analyses will be performed using the SPSS 26.0 software (SPSS Inc., Chicago, IL, USA). We will do an interim analysis when the number of patients reaches half that.

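### The half-course rule for withdrawn patients conflicts with the promised intention-to-treat analysis, and without imputation the AHI comparison is in practice available-case

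*Protocol article*

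**What the plan says.** Two sections of the protocol article bear on who enters the efficacy analysis.

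- Statistical methods: "Outcomes will be analyzed by intention-to-treat and per-protocol". On incomplete data it adds: "Missing data will be considered as missing. Data imputation will not be employed". Groups are compared with a t test for measurement data.
- Adverse events, in a parenthesis after the criteria for discontinuing an individual: "Participants who have exceeded 1/2 of the course of treatment will be included in the curative effect analysis".

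The endpoint and schedule come from three places. Primary outcome: "The primary endpoint of the trial is the AHI change determined by nocturnal polygraphy, before and after 3 months of treatment with dapagliflozin". Follow-up and duration of the study gives two visits at the research center, "one before (baseline) and one after (3 months follow-up) the dapagliflozin intervention". Table 2 marks AHI only at visit 1 and visit 4 (day 84 ± 6).

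Patients leave for events after randomisation. Adverse events lists serious adverse reactions, and cases where "the participants had other acute and severe diseases and needed to take emergency measures". Study design adds: "Using ventilators to treat sleep apnea is not allowed; if it is necessary, they will withdraw from the study". The Discussion states that the trial has neither double blinding nor placebo.

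**The concern.** The half-course sentence has a purpose only if patients who did not pass mid-course are treated differently. Membership of the efficacy analysis then depends on how long a patient stayed on treatment, which is known only after randomisation. An intention-to-treat analysis cannot use such a condition. The sentence names no analysis set, so two analysts could build different primary populations from the same protocol.

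A second problem remains even if the sentence was meant for the per-protocol set only. A patient without a day-84 AHI contributes nothing to a t test on the change when nothing is imputed. One ground for leaving, need for a ventilator, is the condition that AHI measures, and staff and patients know the allocation. Losses may therefore differ between arms and be related to the outcome. At stake is whether the primary comparison keeps the protection of randomisation, in a trial where each arm has about 15 patients.

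**Working it through.** **Step 1: the two rules side by side.** Intention-to-treat takes all randomised patients by assigned arm. The half-course rule takes withdrawn patients only if they passed mid-course. The two sets agree only if nobody withdraws in the first half. The text does not confine the second rule to the per-protocol analysis.

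**Step 2: who has a primary-endpoint value.** Half of an 84-day course is day 42. Table 2 shows no AHI at day 28 or day 56. A patient who withdraws after day 42 therefore counts in name but has only a baseline AHI, unless the day-84 recording is still made.

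**Step 3: the plan's own figures.** The sample size section states that "a 8 ± 6 events/h change in AHI events/h between the control and therapy groups was considered clinically relevant", with no change in controls, 90% power, 5% alpha and a 20% loss. Taking 6 as the SD and the test as two-sided:

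- n per arm = 2 × (1.960 + 1.282)² × 6² / 8² = 11.8, rounded up to 12
- total = 24, and 24 / 0.80 = 30

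This matches the stated 30, so the planned loss is 6 of 30.

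**Step 4: what the rules do to six withdrawals.** Let s be the share who leave after day 42 (not given, so assumed). The half-course rule leaves out 6 × (1 − s) and keeps 6 × s in name.

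| s | left out by the rule | kept, but no day-84 AHI | analysed for AHI |
|---|---|---|---|
| 0 | 6 | 0 | 24 |
| 0.5 | 3 | 3 | 24 |
| 1 | 0 | 6 | 24 |

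Without a recording after withdrawal, 24 patients are analysed in every row.

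**Step 5: illustration of overstatement.** Assume 20% loss in each arm, a difference of 8 among those analysed, no change in any control, and an AHI fall of e in dapagliflozin patients who withdrew. The all-randomised difference is 0.8 × 8 + 0.2 × e.

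| e (events/h) | all-randomised difference | 8 overstates it by |
|---|---|---|
| 0 | 6.4 | 25% |
| 4 | 7.2 | 11% |
| 8 | 8.0 | 0% |

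**Step 6: illustration of the opposite direction.** Now let 8 be the true difference in all randomised patients, with changes distributed N(0, 6) in controls and N(−8, 6) on dapagliflozin. Suppose patients whose AHI rises by more than c leave. The mean of those who stay is μ − 6 × φ(z)/Φ(z), with z = (c − μ)/6. For c = 6:

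- controls: z = 1, loss 15.9%, mean −1.73
- dapagliflozin: z = 2.33, loss 1.0%, mean −8.16
- observed difference: 8.16 − 1.73 = 6.43, against a true 8

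With c = 9 the result is 7.21, and with c = 3 it is 5.41. The cut-offs are assumed. The protocol gives no AHI threshold for leaving and no AHI between baseline and day 84, so this shows direction only.

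**The case against.** The strongest reply is that exclusion of early withdrawals is never written. The sentence says who is included, sits in a safety section, and could be a minimum-exposure criterion for the per-protocol set. On that reading nothing conflicts. This is a fair account of what may have been meant, and it is why confining the sentence to the per-protocol set is an adequate repair. The text does not say so, however, and the missing-data rule still makes the intention-to-treat AHI comparison available-case.

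Four stronger readings are tempting, and the documents do not support them:

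- **That the trial has replaced intention-to-treat with a completer analysis.** The promise of intention-to-treat stands in the text. The fault is an unreconciled rule and an available-case result for AHI.
- **That the half-course rule can never work.** Table 2 schedules the Epworth scale and the Minnesota questionnaire at days 28 and 56 as well as day 84. Someone who leaves after day 56 has data on both. The difficulty is confined to outcomes measured only at baseline and day 84, AHI among them.
- **That no recording is ever made at withdrawal.** The article describes none, but it condenses a fuller protocol that is not shown.
- **That the bias has a known sign or size.** Steps 5 and 6 go opposite ways on assumptions of comparable standing. The 20% is a sample-size allowance, and Statistical methods expects low attrition.

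It can also be said that sensitivity analyses belong in an analysis plan. That would hold had the protocol been silent. It rules out imputation expressly, and an analysis plan consistent with it would inherit that.

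**Conclusion.** The point holds. The half-course sentence implies a selection after randomisation, is tied to no analysis set, and conflicts with the promised intention-to-treat analysis. Separately, with AHI scheduled twice and no imputation, the intention-to-treat AHI comparison rests on patients who have a day-84 recording: about 24 of 30 at the planned loss, if none is made after withdrawal.

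Bias is possible because need for a ventilator is both a ground for leaving and related to the outcome, in an unblinded trial. Its direction and size cannot be derived from the documents. The range of 6.4 to 8.0 against 8 among those analysed assumes equal 20% loss, unchanged controls, and a fall of 0 to 8 in withdrawn dapagliflozin patients. Loss of worsening controls would instead understate the effect.

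**What to change.** 1. Delete the half-course sentence, or state that it defines the per-protocol set only.
2. State that the primary analysis is intention-to-treat in all randomised patients by assigned arm, with per-protocol as a sensitivity analysis.
3. Separate stopping treatment from leaving follow-up. Seek the already planned day-84 polygraphy whatever the treatment status, where the patient consents. State in advance how an AHI recorded after ventilatory support has begun is handled, since it reflects that support as well as the assigned arm.
4. Replace the ban on imputation with at least one missing-data sensitivity analysis for the AHI change, such as multiple imputation or a tipping-point analysis. Count patients without an AHI as non-responders in the 20% and 50% outcomes.

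The clinical withdrawal rules stay as they are, and no study recording is to be placed ahead of necessary treatment. Bringing the recording forward to the moment of withdrawal is not proposed, because it would change the 3-month endpoint.

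The cost is a few sentences of wording, follow-up recordings for a few patients from among those already planned, and a little more analysis. Enrolment was ongoing when the article was submitted, and a missed day-84 recording cannot be recovered later, so the change is worth making early.
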